Abbott and co-workers conducted two series of studies on individuals with obesity and/or non-insulin-dependent diabetes mellitus (NIDDM) to assess the effects of this dietary recommendation on both lipoproteins and their metabolism as well as on insulin secretion and action and energy expenditure (Abbott et al 1990a, 1990b). Both series compared a diet high in saturated fat with a diet high in complex carbohydrates and fiber. Calories and proportion of protein were constant. In the first set of studies, the aim was to examine the effect of replacement of saturated fat with complex carbohydrate in a regimen with conventional foods that would closely approximate foods expected to be used and recommended to diabetic patients. In the second regimen, more extreme difference between carbohydrate content and fat content was investigated using a dietary change that would approximate the contrasts between traditional diet of Native Americans or other cultures and a modern westernized diet.

The effects on lipoproteins included consistent decreases in total and LDL cholesterol (av 10%), minimum to no change in HDL cholesterol, and insignificant changes in total or VLDL triglycerides or 24-h triglyceride profiles. Changes in total and LDL cholesterol required 3-4 wk to reach equilibrium. Metabolic studies used to elucidate the reasons for the decrease in LDL cholesterol confirmed no stimulation of VLDL triglyceride or apolipoprotein B (apoB) production on the high-carbohydrate diet. The decrease in LDL appeared to be due to decreases in mechanisms that convert VLDL to LDL and increased activity of LDL apoB clearance. In the study with traditional foods, where dietary carbohydrate was 70% and fat only 15%, there was no improvement in glucose tolerance. It was accompanied by an improvement in glucose-mediated glucose disposal and insulin secretion. In individuals having a wide range of obesity and glucose tolerance, substitution of complex carbohydrates for saturated fat has beneficial effects of lowering LDL cholesterol and possibly improving glucose tolerance and insulin secretion but without having any adverse effects on lipoprotein metabolism or energy expenditure (Howard et al 1991).

In the earlier stages of progression of this disease, insulin resistance prevails, especially because most patients are overweight; β-cell function, while probably impaired, remains relatively responsive. However, because most of these patients are overweight, the primary aim of dietary therapy is to restrict total calories to achieve weight reduction. Thus, regardless of the composition of the diet, all nutrients (fat, carbohydrate and protein) are restricted. If we assume that the average obese patient with IGT is consuming 3000 kcal/day, for the purpose of weight reduction, and 1800-kcal diet can be recommended (Grundy 1991). Even if this diet has a high percentage of total fat (40%) and is relatively enriched in monounsaturated fatty acids (26%), the total fat will still have to be reduced from 133 to 80g/day. Therefore, on the weight-reduction diet, even monounsaturated fatty acids are curtailed. If a 25%-fat diet is used for weight reduction, total fat is cut further to 50g/day. The difference in fat intake between these two weight-reduction diets is equivalent to ~ 2 tbl an oleic-rich oil (e.g., olive oil or canola/rapeseed oil) or ~ 270 kcal/day from fat. There would appear to be little difference between these two 1800-kcal diets for obese patients with IGT, and personal preference may determine which diet to use.

A one-year randomized clinical trial of non-pharmacologic treatment of nondiabetic adults with hyperinsulinemia was recently carried out (Nilsson, et al, submitted). One group of subjects received intensive lifestyle intervention and the other was followed passively. Those in the active treatment were seen in groups of approximately 8 subjects. Each group met monthly at evening sessions, with the guidance of a group leader (nurse, dietician or physiotherapist). Each session lasted 1-2 hours, and participants were encouraged also to meet between sessions. On four occasions special physical activity (outdoor walking for two hours) was offered to all participants and their relatives. Special physical activity sessions were also offered biweekly to the most sedentary subjects. Participation in other activites of sport organizations were strongly recommended when appropriate. Special guided tours in local supermarkets, cooking demonstrations, and distribution of free olive oil were used to promote adherence to a healthier lifestyle. Group dynamic techniques were used to help participants join together and encourage each other.

A prudent low-fat, high-fiber diet was recommended, and dieticians performed four-day dietary recordings, at start and after one year, for evaluation of personal eating habits, as well as for individual counselling. A computer program for nutrients was used. Dietary recommendations included total fat <30% of daily energy intake, a high P/S ratio (0.8-1.0), and an increased consumption of mono- and polyunsaturated fatty acids. Intake of cholesterol was <200 mg/day. Dietary fiber was recommended at 30 g/day, mostly of the water-soluable type in oat and bean products, fruits, and vegetables. Fatty cold-water fish (salmon, mackerel) was recommended, and dietary salt reduced. Caloric intake was reduced in those with body mass index 27 kg/m2 and abdominal obesity (waist/hip 0.95). Physical activity was individually encouraged, based on improvements in ordinary life habits (walking, cycling, gardening). Aerobic activities of a dynamic, submaximal and long duration were preferred. Alcohol was accepted in reasonable amounts but overconsumption was discouraged.

In the active group, mean body weight decreased by 2.2 kg during the year, compared with a decrease of 0.1 kg in the passive group. Blood pressure, fasting plasma insulin and C-peptide concentrations also fell significantly in the intervention group only. In contrast, two-hour post-load blood glucose increased in the passive group but did not change significantly in the intervention group. Thus this study demonstrates the feasibility of the type of diet-exercise intervention proposed in this application, and its effect on body weight and glucose and insulin metabolism in nondiabetic Swedish subjects.

2.3.2 Justification for performance in Finland. The proposed study could potentially be conducted in many different locations, but there are several distinct advantages of performing the study in Finland by the applicant investigators:

1) The success of such therapy appears to be higher in Finland than elsewhere (e.g. England or North America), perhaps because of differences in social structure, with much more willingness to conform to prescribed behavior.

2) It is relatively easy in Finland to organize population screening programs and follow persons long term because of the universal use of personal identification numbers coupled with access to names, addresses, and vital status, and because of the social attributes referred to above.

3) Among the group of investigators, there is considerable expertise and experience not only in the conduct of pharmacologic and behavioral clinical trials, but also in diabetology, epidemiology, and biostatistics.

Table 2.1 STUDIES OF THE CUMULATIVE INCIDENCE (CI) OF DIABETES IN IGT

Study Definition Treat- N at Followup CI 5yr CI#

(Reference) of IGT ment risk (years) (%) (%)

Whitehall, UK 2hr BG Yes/No* 204 5 13 13

(Jarrett, 1979) =6.7-11.0

Malmöhus, Sweden local No 59 10 29 15

(Sartor, 1980) criteria

" " " Yes 147 10 12 6

" WHO No 22 10 32 16

" WHO Yes 25 10 20 10

Bedford, UK 2hr cap BG Yes/No* 241 10 15 8

(Keen, 1982) =6.7-11.1

Nauru WHO No 51 6 25 21

(King, 1984)

Tokyo, Japan 2hr BG No 288 9 17 9

(Kadowaki, 1984) =7.2-13.3

Israel NDDG criteria No 83 3 11 18

(Modan, 1986) for nondiag-

nostic or IGT

Pima Indians, USA WHO No 384╪ 5 25 25

" " " " " 10 61

(Saad, 1988a)

Malmö, Sweden WHO No 56 5 21 21

(Eriksson, in press) " Yes 161 5 11 11

Malta

(Schranz 1989) WHO No 75 6 31 26

San Antonio, USA WHO No 61 8 19 12

(Haffner, 1990)

Finland WHO No 234 5 12 12

(Stengård 1992)

#Estimated 5-year cumulative incidence by linear interpolation from actual follow-up period and cumulative incidence.

*In these clinical trials those subjects treated or not treated with hypoglycemic drugs were pooled as this treatment variable had no significant effect on the outcome.

╪Number at baseline, follow-up period varied between subjects.

CHAPTER 3. STUDY DESIGN

3.1 STUDY PURPOSE AND DESIGN SUMMARY

3.1.1 Purposes. The Diabetes Prevention Study (DPS) has three major purposes:

1) to assess the efficacy of a special diet-exercise program in preventing or delaying the onset of type 2 diabetes in persons with IGT, and

2) to study the risk factors for progression to diabetes in persons with IGT.

3) to assess the effects of the intervention on atherosclerotic vascular disease.

3.1.2 Primary Endpoint. The primary endpoint is diabetes, as defined in detail in Chapter 7.

Subjects will remain in the study and be followed until the end of the study or death, whichever occurs earlier. Study treatments will be continued until the end of the study, death, or the occurrence of diabetes, whichever occurs earlier.

3.1.3. Secondary endpoints. Subjects will also be monitored for the following secondary endpoints as defined in detail in Chapter 7:

1) Fatal or non-fatal myocardial infarction or sudden cardiac death.

2) Angina pectoris.

3) Intermittent claudication.

4) Stroke.

5) Death from any cause.

3.1.4 Subjects. Subjects with IGT will be found by population screening. A total of 560 subjects at several Clinical Centers will be treated and followed for at least five years. Each subject will be randomly allocated to a special or standard diet-exercise program. A Central Laboratory will make biochemical measurements, and a Coordinating Center will coordinate study activities and provide central data management and statistical support.

3.2 SUBJECT ELIGIBILITY AND EXCLUSION CRITERIA

3.2.1 Definitions of diabetes and IGT. The classification of and diagnostic criteria for diabetes and other categories of glucose tolerance will be based on criteria adopted by the World Health Organization (WHO), (World Health Organization, 1985). According to WHO criteria, the diagnosis of diabetes may be established on the basis of:

1) casual plasma glucose concentrations  11.1 mM (200 mg/dl) on one occasion with symptoms or on two without,

2) fasting venous plasma glucose concentrations  7.8 mM (140 mg/dl) on more than one occasion, or

3) oral glucose tolerance tests meeting the criteria shown in Table 3.1. IGT is diagnosed when the criteria for diabetes are not met, but the 2 hour post‑load plasma glucose is from 7.8 to 11.0 mM (140 to 199 mg/dl).

TABLE 3.1. DIAGNOSTIC VALUES FOR THE ORAL GLUCOSE TOLERANCE TEST

ACCORDING THE WORLD HEALTH ORGANIZATION (WHO)

Venous plasma glucose concentration

mM mg/dl

IGT Fasting < 7.8 <140

and 2 hour 7.8‑11.0 140‑199

Diabetes Fasting > 7.8 >140

or 2 hour >11.1 >200

3.2.2 Eligibility and exclusion criteria. To be eligible for

participation in the DPS, subjects must meet the following eligibility criteria. Subjects will have IGT, will be aged 40-64 years, and will not have a history of diabetes. The full eligibility and exclusion criteria are given in Section 5.1.

3.3 SCREENING FOR IGT

The screening procedure is described in Section 5.2.

3.4 ELIGIBILITY CRITERIA

There will be a comprehensive examination to determine eligibility.

To remain eligible, a subject must meet no further exclusion criteria upon review of results of the medical evaluations performed at the screening examinations (Section 5.3).

A subject not meeting the eligibility criteria will be discharged from the study, after being told that he/she is ineligible because of medical contraindications. All such exclusions and their reasons will be recorded as part of the study data.

3.5 REGISTRATION, RANDOMIZATION, AND STRATIFICATION

3.5.1 Treatment assignment and registration. Assignment will be issued by the Clinical Center which will register enrollment of subjects upon verification that all eligibility criteria have been met.

3.5.2 Randomization to treatment. Subjects will be randomly allocated to special or standard diet-exercise program in the following way:

Group 1: Special diet - exercise

Group 2: Standard diet - exercise

3.5.3 Stratification. Randomization will be stratified by 1) Clinical Center and 2) the 2-hour post-load glucose obtained during the OGTT:

o Stratum 1: venous plasma glucose = 7.8-9.4 mM (140-169 mg/dl)

o Stratum 2: venous plasma glucose = 9.5-11.0 mM (170-199 mg/dl)

3.5.4 Registration. Subjects are enrolled in the DPS as soon as they are registered by the Clinical Center. The Clinical Center will promptly register a subject upon verification that all eligibility criteria have been met. A registration number (and treatment assignment) is given to the subject according to the randomization list.

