3.7 MASKING

3.7.1 The diet-exercise intervention will be only partly masked. This assignment can obviously not be masked from the subjects or from those Clinical Center personnel who counsel the subjects on their diet or exercise programs. However, all laboratory personnel, including those performing the glucose tolerance test, and the Endpoints Committee (Chapter 8) will be masked.

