5.1.2 Exclusion criteria

o Previous diagnosis of diabetes other than gestational diabetes (diabetes first diagnosed during a pregnancy) which has not persisted after pregnancy

o Previous treatment for IGT other than with routine dietary and health advice (persons previously given intensive diet or exercise treatment for IGT or other metabolic conditions such as hyperlipidemia will be excluded)

o Participation in a regular program of vigorous physical exercise

o A myocardial infarction or a by-pass operation less then 1 year ago o Hypersensitivity to diet or exercise program

o Chronic illness that makes 6-year survival improbable, or illness which requires or is likely to require treatment known to affect glucose tolerance (e.g. corticosteroid drugs)

o Mental or medical characteristics that are likely to interfere with informed consent, compliance with diet, exercise, or long-term follow-up

These eligibility and exclusion criteria are specified for the following reasons. The age range of 40-64 years is chosen to include a target population old enough for IGT to have a substantial prevalence to make screening feasible and young enough that the mortality rate will not cause many censored observations when development of diabetes is the primary endpoint. Pregnancy is to be avoided because of its effects on glucose tolerance and interference with treatment procedures. Subjects must be overweight and not participating in a vigorous exercise program, because weight loss and exercise will be components of the diet-exercise intervention. As first occurrence of diabetes will be the primary endpoint, it must not already have been diagnosed at entry. Previous treatment of IGT (such as by diet or exercise) may have established permanent changes in behavior which would make randomization to the standard diet-exercise group impractical. Entry of patients treated with drugs known to affect glucose tolerance would confuse interpretation of findings. The other medical contraindications are to avoid randomizing patients who would be unlikely to be able to maintain randomized treatment throughout the study.

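### The Clinical Center both decides enrolment and issues the assignment from the list, and nothing in the protocol conceals the next assignment

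*Protocol*

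**What the plan says.** Protocol section 3.5.1 gives the release of the arm to the site: "Assignment will be issued by the Clinical Center which will register enrollment of subjects upon verification that all eligibility criteria have been met". Section 3.5.4 repeats that the site registers: "The Clinical Center will promptly register a subject upon verification that all eligibility criteria have been met". It then ties registration to the arm in one step: "A registration number (and treatment assignment) is given to the subject according to the randomization list". Under section 3.5.3, "Randomization will be stratified by 1) Clinical Center and 2) the 2-hour post-load glucose obtained during the OGTT", with two glucose levels.

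Section 4.2.2 places the physician's eligibility examination, randomization and arm-specific counselling in the same enrollment visit. Among the exclusions in section 5.1.2 is one that calls for judgement: "Mental or medical characteristics that are likely to interfere with informed consent, compliance with diet, exercise, or long-term follow-up". On masking, section 3.7.1 states: "This assignment can obviously not be masked from the subjects or from those Clinical Center personnel who counsel the subjects". It masks laboratory and glucose-tolerance personnel and the Endpoints Committee.

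Section 3.1.4 provides a central body: "a Coordinating Center will coordinate study activities and provide central data management and statistical support". Neither that section nor section 3.5 gives it a part in allocation. For couples, the text after the exclusion list in section 5.1.2 randomizes only the first spouse; the other receives the same arm.

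**The concern.** Randomization protects the comparison only if whoever decides on enrolment cannot know or infer the next arm. If they can, a borderline subject can be excluded, deferred or taken out of turn according to the arm that is due. The arms may then differ in prognosis before treatment begins.

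Here the deciding and the releasing sit in one centre, in one visit, in a trial of an unmasked behavioural intervention. The masked laboratory and Endpoints Committee protect outcome assessment; they do nothing for allocation. Adjustment under section 8.2 can address measured baseline factors, but its list does not include motivation or expected compliance. Those are traits that a judgement-based exclusion turns on.

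**Working it through.** The point is procedural, and the protocol gives no figure of its own for it. The check is a reading of the allocation steps, followed by two illustrations under stated assumptions.

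**Allocation steps**

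1. Who verifies eligibility and registers: the Clinical Center (3.5.1, 3.5.4).
2. Who issues the arm: the Clinical Center (3.5.1).
3. From what: a randomization list (3.5.4). Its holder, form and block size are not stated.
4. Whether registration is locked before the arm is seen: not stated; number and arm are given together (3.5.4).
5. Whether eligibility leaves room for judgement: yes, in part (5.1.2).
6. Who at the centre knows earlier assignments: at least the counselling staff (3.7.1).
7. Whether a party independent of enrolment takes part: none is named, although a Coordinating Center exists (3.1.4).
8. Whether any arm is known in advance by rule: yes, that of a second spouse who is enrolled after the first was assigned (5.1.2).

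Nothing in items 1 to 7 keeps the next assignment from those who decide enrolment. Item 8 is foreknowledge written into the protocol.

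**Illustration 1: guessing from past assignments.** Assume permuted blocks of size 2h, a hidden list, known past assignments in the stratum, and a guesser who always names the arm with more places left in the block (a coin toss if equal). Expected correct guesses per block = h + (4^h / C(2h, h) − 1)/2. Share of assignments that are certain = 1/(h + 1).

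- Block of 2: 1 + (4/2 − 1)/2 = 1.5 of 2, or 75%; certain 50%.
- Block of 4: 2 + (16/6 − 1)/2 = 2.83 of 4, or 71%; certain 33%.
- Block of 6: 3 + (64/20 − 1)/2 = 4.1 of 6, or 68%; certain 25%.
- Block of 8: 4 + (256/70 − 1)/2 = 5.33 of 8, or 67%; certain 20%.

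If the list can be seen, every next assignment is known.

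**Illustration 2: what an imbalance would do to the test.** Inputs: 250 per arm (half of the 2N = 500 in section 3.8, which reproduces with its p1 = .28 and p2 = .175) and a 5-year risk of 28%. Assume no treatment effect, and arms that differ by d in underlying risk, centred on 28%. The standard error under equal risks is √(2 × 0.28 × 0.72 / 250) = 0.0402, and it changes little for small d. The two-sided 5% test rejects with probability of about Φ(d/0.0402 − 1.96) + Φ(−d/0.0402 − 1.96).

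- d = 1 point: 5.7%
- d = 2 points: 7.9%, from Φ(−1.46) + Φ(−2.46)
- d = 3 points: 11.6%
- d = 5 points: 23.8%

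These values of d are assumed. The protocol gives no basis for choosing among them, or for expecting any of them.

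**The case against.** The strongest reply is that the protocol is silent on concealment, which is not the same as having none. It does not say who at the centre holds the list, whether it is open or sealed, or that the physician who judges eligibility ever sees it. The Manual of Operations mentioned in section 3.9 is not shown and may cover this. Issue by the site is not in itself a fault either: sealed envelopes opened at the centre would fit the wording of 3.5.1.

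There are also partial protections. Verification precedes registration, and registration is to be prompt. Section 3.4 has exclusions and their reasons recorded, which leaves a trail for steering by exclusion, though not by delay. Most entry criteria are measured: glucose values, body mass index, age and the walking test. Stratification limits imbalance in 2-hour glucose, a strong predictor by section 2.2.2, and section 8.2 allows covariate adjustment.

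All of this stands, and it limits the claim. A reader might infer that the next allocation can in fact be foreseen, that the whole centre is unmasked, that the strata are small, or that motivated low-risk subjects would end up in the special arm. The documents support none of these.

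- Access to the list is not described.
- Only counselling staff are said to be unmasked; under section 6.1 a dietitian gives the dietary advice, while under 4.2.2 a physician examines for eligibility.
- The protocol speaks only of several centres. With an assumed 4 to 6 equal centres and two equal glucose levels, strata would hold 560/8 = 70 to 560/12 = 47 subjects, and guessing depends on block size, which is not given.
- Staff might equally favour those in greatest need for the special arm, which would bias the comparison the other way.

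The reply does not remove the core of the point. Sections 3.5.1 and 3.5.4 do fix a procedure, and that procedure assigns release of the arm to the party that decides enrolment, with no stated safeguard. If the Manual contains one, section 3.5 should state it.

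**Conclusion.** The concern holds in this form: the Clinical Center, whose counselling staff are unmasked, verifies eligibility, registers and issues the arm from the list, and the protocol contains nothing that conceals the next assignment from those who decide enrolment. Selection bias is therefore not prevented. That is short of saying that it is expected.

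Its size and direction cannot be estimated from the document. The guess rates of 67% to 75% rest on assumed permuted blocks and known past assignments. The false-positive rates of 5.7% to 23.8% rest on assumed imbalances of 1 to 5 points. Both show only why concealment matters at this sample size.

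For a second spouse enrolled after the first was assigned, foreknowledge is certain by rule, and central release alone would not cure it. This is an inexpensive improvement that should be made before enrolment starts, since concealment cannot be restored afterwards.

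**What to change.** Amend sections 3.5.1 and 3.5.4 along these lines:

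1. The Clinical Center submits the completed eligibility form and glucose stratum to the Coordinating Center.
2. The Coordinating Center alone holds the list and keeps any block sizes undisclosed to the centres.
3. It registers the subject irrevocably, and only then releases the assignment.
4. Where this is not feasible, use sequentially numbered, sealed, opaque envelopes prepared by the Coordinating Center and opened after registration.

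In the couples paragraph of section 5.1.2, add that where both spouses are candidates, the eligibility of both is verified and registered before the first spouse's assignment is released.

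The cost is one call or envelope per subject, about 560 over the two-year enrolment, and a small delay at the enrollment visit. Sample size and endpoints are unaffected.
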